### Statistical Analysis and Power Assessment

Descriptive statistics, including means, standard deviations, frequencies, and percentages, will be used to describe the experimental and control groups on the baseline demographic variables to achieve our first objective, which is to conduct a power analysis of the required sample size to test the difference between the experimental and controls groups at the postintervention measurement. We will test the difference between experimental and control groups on continuously and normally distributed outcome measures using analysis of covariance, with the dependent variable being the postintervention measurement of the outcome, the covariate being the preintervention measurement, and group membership being the between-participant effect. Descriptive statistics, including measures of skewness and kurtosis, will be used to assess departures from the assumptions of a normal distribution of responses. If the distribution contains extreme observations, a robust ANCOVA statistic will be adopted [49]. To test differences between experimental and control groups on discrete outcomes, such as number of times participants feel dizzy during their daily activities, we will use a Poisson regression model, with the dependent variable being the number of relevant events, the covariate being the preintervention measurement, and group membership being the between-participant effect.

To analyze the longitudinal data associated with the second objective, we will use a regression model with time as the random factor [50]. This model will be adopted because it accounts for clustering of repeated measurements within study participants and uses all available longitudinal data (ie, it does not result in case-wise deletion of study participants due to missing observations). Prior to applying this model to the data, we will conduct descriptive analyses of the proportion and pattern of missing data. To assess model fit, we will use penalized measures of the log of the likelihood function, including the Akaike Information Criterion and Bayesian-Schwarz Information Criterion. Initially we will fit a model with only a random intercept for time; subsequently, we will also consider a random slope. The intraclass correlation and the proportion of variation explained by the random effects will be calculated.

The pilot data showed a standardized effect size of .80. Assuming the number of model covariates to be 3, the proportion of variance explained by these covariates to be 10%, and a two-tailed test of the null hypothesis of no group difference at alpha=.05, we calculated that a sample size of 46 is required. Given an expected attrition rate of 20% over the study observation period for objective 2, we propose to recruit a total of 56 individuals to participate, with equal numbers for the treatment and control groups.

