### Recording and Data Analysis

The following information will be collected at baseline prior to start of the interventions: age, gender, work history, history of disease/injury process, and current medications. The assessor will be blinded to participant assignments. The primary outcome measures of the study include measurement of dynamic visual acuity, balance performance, and DHI. The secondary outcome measures of the study include gaze performance and gait analysis.

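### The Poisson model for count outcomes such as dizziness episodes makes no allowance for overdispersion, so its group test is likely to reject too often

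*Protocol article*

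**What the plan says.** The section Statistical Analysis and Power Assessment separates two kinds of outcome for the comparison between groups.

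- **Continuous outcomes** go into an analysis of covariance on the baseline value. Skewness and kurtosis are examined, and there is a fallback: "If the distribution contains extreme observations, a robust ANCOVA statistic will be adopted".
- **Counts**, described as "discrete outcomes, such as number of times participants feel dizzy during their daily activities", go into a log-linear count model: "we will use a Poisson regression model, with the dependent variable being the number of relevant events, the covariate being the preintervention measurement". Group is the other term. No dispersion check, scale parameter, robust variance or alternative count model is mentioned.

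The only other statement on adequacy of fit is "To assess model fit, we will use penalized measures of the log of the likelihood function". It stands in the paragraph on the longitudinal model for the second objective.

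Recording and Data Analysis lists the outcomes: "The primary outcome measures of the study include measurement of dynamic visual acuity, balance performance, and DHI", and then "The secondary outcome measures of the study include gaze performance and gait analysis". A count of dizziness episodes is in neither list.

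**The concern.** Poisson regression is correct only if all participants with the same baseline count and the same group share one underlying event rate. Recurrent symptoms seldom behave like that: some people have hardly any episodes and others have many. One baseline count measures a person's rate with error, so adjusting for it is unlikely to remove all variation between people. Whatever remains pushes the variance above the mean, while the model goes on computing standard errors as if the two were equal.

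The group test on such an outcome would then reject a true null hypothesis more often than stated, and its confidence interval would be too narrow. The trial postulates that the home programme improves dizziness more than clinic care, so a falsely significant dizziness count could be read as support for that claim.

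**Working it through.** **Inputs.** From the article: Poisson model with baseline and group; "a two-tailed test of the null hypothesis of no group difference at alpha=.05"; 46 participants required and 56 to be recruited, in equal groups. Not in the article: any mean, variance or dispersion for a count outcome. The dispersion values below are therefore assumptions, shown as a range.

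**The plan's own figure.** The article states "The pilot data showed a standardized effect size of .80", with covariates explaining 10% of the variance. It does not state the power, so 80% is assumed. Per group, n = 2 × (1.96 + 0.842)² × (1 − 0.10) / 0.80² = 2 × 7.85 × 0.90 / 0.64 = 22.1, rounded up to 23, or 46 in total. The stated 46 is reproduced. It rests on a standardized difference in a continuous outcome, so it neither supports nor contradicts the count analysis.

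**Why the variance exceeds the mean.** Let person i have event rate λ, and let x be the baseline count. Then Var(Y | x) = E(λ | x) + Var(λ | x). The Poisson model keeps only the first term. Write φ for the ratio of the true conditional variance to the mean. The true standard error of the group coefficient is then about √φ times the one that the model reports.

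**True size of the nominal 5% test.** Error = 2 × [1 − Φ(1.96/√φ)].

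| φ | √φ | 1.96/√φ | true two-sided error |
|---|---|---|---|
| 1 | 1.00 | 1.960 | 5.0% |
| 1.5 | 1.22 | 1.600 | 11.0% |
| 2 | 1.41 | 1.386 | 16.6% |
| 3 | 1.73 | 1.132 | 25.8% |
| 4 | 2.00 | 0.980 | 32.7% |

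**Does baseline adjustment or sample size rescue it?** Gamma-Poisson counts were simulated with no group effect, equal allocation and 600 runs per scenario. The Monte Carlo standard error at a true 5% is √(0.05 × 0.95 / 600) = 0.9 percentage points.

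- With 46 participants, mean 5, between-person rate variance 0.5 (relative to a mean rate of 1) and latent baseline-to-post correlation 0.6, the residual φ was about 2.7. The group coefficient varied 1.67 times as much as the model's standard error implied. The Poisson test rejected in 24.8% of runs with the raw baseline count and in 23.5% with log(count + 1).
- With the correlation raised to 0.9, the rates were 19.7% and 15.8%. Baseline adjustment helps but does not cure the problem.
- With 56 participants and correlation 0.6, the rate with the raw baseline was 26.2%. A larger sample does not help.
- Over all overdispersed scenarios at 46 participants (means 2, 5 and 10), the Poisson test with the raw baseline rejected in about 8% to 51% of runs. Quasi-Poisson with a t reference rejected in about 4% to 7%, and the robust variance in about 5% to 8%. Both corrected analyses used log(count + 1) as covariate.
- With no overdispersion at 46 participants, Poisson with the raw baseline rejected in about 4% to 5% and quasi-Poisson also in about 4% to 5%. The correction does no harm when it is not needed.

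**The case against.** **Materiality.** The count appears once, as an example. It is not a listed outcome, the article describes no instrument or counting period for it, and the sample size does not use it. The trial is a pilot. All of this stands and limits the weight of the point.

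**Condensed reporting.** A journal article may leave the variance estimator to a fuller plan, and naming Poisson regression for a count is not wrong in itself. This stands in part: a fuller plan may already contain the correction. But the article does not merely stay silent. It fixes the model and its terms, and it provides for failed assumptions in the continuous analysis and for fit assessment in the longitudinal one.

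**Unknown dispersion.** If counts were not overdispersed after adjustment, the planned test would be valid. This also stands, and it makes the conclusion conditional.

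A reader might infer three stronger things that the article does not support:

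- That the standard errors are certainly too small. No count data are given, so this is likely but not shown.
- That a few participants with high baseline counts would dominate the fit under the log link. The article does not say on what scale the baseline enters. In the scenarios above, the Poisson error rate was at most about 5 percentage points lower with the logged baseline than with the raw one.
- That the primary dizziness result is at risk. The listed dizziness measure is the DHI, a questionnaire score, and nothing assigns the event-count model to it.

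**Conclusion.** The point holds as a conditional defect of modest reach. The article commits to a Poisson model for counts and protects it against nothing, while recurrent symptom counts are likely to stay overdispersed after adjustment for one baseline count. At assumed variance-to-mean ratios of 1.5 to 4, the true two-sided error is 11% to 33% against a nominal 5%, and the intervals are too narrow by a factor of 1.22 to 2.00. At a ratio of 1 there is no inflation. The size rests entirely on the assumed ratio and on the use of model-based standard errors, which is what a Poisson regression gives unless something else is specified. The analyses of the listed primary and secondary outcomes and the sample size are not shown to be affected.

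**What to change.** In Statistical Analysis and Power Assessment, replace the Poisson model for count outcomes with quasi-Poisson regression (scale estimated from the data, t reference), or with Poisson regression and a small-sample robust variance. Negative binomial regression is an acceptable alternative, but its performance at this sample size was not checked here. Keep the preintervention count and group in the model.

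The cost is one sentence and somewhat wider intervals, by about √φ where counts are overdispersed. Where they are not, almost nothing is lost: with 46 participants and three coefficients, the t reference on 43 degrees of freedom uses 2.02 in place of 1.96, an interval about 3% wider. Neither an offset nor a change to the outcome lists is needed to cure this defect.

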## Methods

New telerehabilitation technologies (ie, digital media and innovative computer input devices) may improve clinical outcomes by making rehabilitation more motivating, accessible, and ecological. The research objectives of this study are

1. Compare the therapeutic effectiveness of a home game-based rehabilitation program to standard care delivered in an outpatient physical therapy clinic on measures of balance, gaze control, dizziness, and health-related quality of life; and

2. Examine the time course of change electronic gaze performance measures of participants in the home program.

It is postulated that the home game-based rehabilitation program will result in greater improvement in gaze control, dynamic balance control, and dizziness than a typical outpatient physical therapy regimen.

A randomized, controlled, single-blind pilot trial will be conducted (University of Manitoba Human Research Ethics Board, reference number: H2014:149).

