#### Gait Analysis

A gait analysis will be conducted to examine whether the exercise program transfers to improvements in walking function. A treadmill instrumented with a pressure mat (Vista Medical, CA, USA) will be used to record vertical foot forces for each step during walking trials of 1 minute at 0.9 m/s, and thus include data for 30 consecutive steps [35,48]. The following spatiotemporal gait variables (average and coefficient of variation through 30 consecutive steps) will be computed: step and swing durations, single support times, step width, and step length.

Participants will be asked to complete daily exercise logs. The study therapist will contact each participant through phone or email on a weekly basis to obtain the exercise logs.

Interventions will begin within 1 week of the baseline assessment (primary and secondary outcome measures). The postintervention assessment will be conducted within 1 week of the final intervention session.

Participants in the experimental group will be given the visual tracking game application for home use. The game software automatically logs reference and head cursor coordinates (gaze performance) during the visual tracking task and saves the data to a coded and time-stamped computer file. Participants will be asked to play the tracking task in standing position at the beginning of every training session. This will involve 3 short tests of 45 seconds each at 3 tracking speeds. The clients can either email the data files to the investigator, or save them on a provided flash drive, which should be returned at a follow-up visit. This will allow us to perform a within individual trend analysis of up to 48 repeated measures for the experimental group.

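### The objective 2 model names time as the random factor, which contradicts its stated purpose of handling clustering within participants; participant should be the grouping factor

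*Protocol article*

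**What the plan says.** The second research objective in Methods is to "Examine the time course of change electronic gaze performance measures of participants in the home program". The data come from home logging of the tracking task. The end of the Gait Analysis section says that this permits "a within individual trend analysis of up to 48 repeated measures for the experimental group".

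Statistical Analysis and Power Assessment then gives the model: "we will use a regression model with time as the random factor". The fitting order is "Initially we will fit a model with only a random intercept for time; subsequently, we will also consider a random slope". The reason for choosing the model is that "it accounts for clustering of repeated measurements within study participants". AIC and BIC are to assess fit, and "The intraclass correlation and the proportion of variation explained by the random effects will be calculated". Participant is not named anywhere in that paragraph as a random or grouping factor.

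**The concern.** A random intercept for time makes different participants measured at the same session correlated with each other. It creates no correlation between sessions of the same participant. These data are up to 48 measurements on each person, so within-person correlation is their main feature, and it is the feature that the model is said to handle. The text makes time random twice, in the model statement and in the fitting order, so it does not look like a single slip.

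An analyst has to code one grouping factor, and the only one named is time. If that is coded, two results for objective 2 are affected: the standard error of the trend and the intraclass correlation.

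**Working it through.** **The plan's own figures.** No sample size, variance or power is stated for objective 2. The only sample-size figure belongs to the group comparison. It reproduces if 80% power is assumed (power is not stated): per arm 2 × (1.96 + 0.84)² × (1 − 0.10) / 0.80² = 22.1, rounded up to 23, so 46 in total; and 46 × 1.2 = 55.2, rounded up to 56. This does not depend on the objective 2 model.

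**Inputs for the check.** From the document: 56 participants in equal arms, so J = 28 in the experimental arm, and up to T = 48 repeated measures. Assumed, because the document gives neither: within-participant ICC ρ of 0.3 to 0.7, and between-participant SD of total change τ of 0 to 0.5, both with intercept plus residual variance set to 1. Complete data and no true mean trend are also assumed.

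**Formulas.** Let time run evenly from −0.5 to 0.5. Then Sxx = T(T + 1) / [12(T − 1)] = 48 × 49 / (12 × 47) = 4.170.

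- True SE of the mean slope: √{[τ² + (1 − ρ)/Sxx] / J}
- SE reported with a random intercept for time and no participant term: about √{[1 + τ²·Sxx/T] / (J·Sxx)}

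The first depends on ρ; the second does not, because that model cannot separate participant variance from residual variance.

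*Example, ρ = 0.5:*

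- τ = 0: true SE √(0.5/4.170/28) = 0.0654; reported SE √(1/116.8) = 0.0925; ratio 1.41.
- τ = 0.5: true SE √[(0.25 + 0.120)/28] = 0.1149; reported SE √(1.0217/116.8) = 0.0935; ratio 0.81.

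**Simulation, 4000 data sets per setting.** The time-grouped model includes a linear time trend.

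| ICC ρ | Slope SD τ | Reported SE / true SE | Type I error, time-grouped model |
|---|---|---|---|
| 0.3 | 0 | 1.18 | 2.1% |
| 0.3 | 0.25 | 1.02 | 4.7% |
| 0.3 | 0.5 | 0.77 | 13.5% |
| 0.5 | 0 | 1.39 | 0.8% |
| 0.5 | 0.25 | 1.11 | 3.0% |
| 0.5 | 0.5 | 0.80 | 11.7% |
| 0.7 | 0 | 1.81 | 0.1% |
| 0.7 | 0.25 | 1.31 | 1.2% |
| 0.7 | 0.5 | 0.85 | 10.2% |

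An analysis of participant-level slopes gave 4.8% to 5.5% in all nine settings. The ICC from the time-grouped model was about 0 throughout, against the assumed 0.3 to 0.7.

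**Larger slope variation.** With intercept SD 1, residual SD 1 and total-change SD 1 (1/√2 = 0.71 on the scale above), the time-grouped model rejects about 22% of the time. With intercept SD 0.5, residual SD 1 and total-change SD 2 it rejects about 55%. The last case is extreme, since the SD of change is four times the intercept SD.

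**Participant intercept without a slope.** Once slopes vary (τ = 0.25 or 0.5), this model also understates the SE: its ratio to the true SE is 0.49 to 0.86. That is why the restated model needs the slope term as well as the correct grouping factor.

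**The case against.** The strongest reply is that the paragraph describes an ordinary participant-level growth model in loose language. It gives participant clustering as its purpose, it wants to avoid deleting participants with missing observations, and it plans a random slope and an intraclass correlation. The Gait Analysis section speaks of trends within individuals. If sessions were the groups, time would be constant within each group, so a random slope on time would have no meaning. This is a good argument about what was intended. It does not remove the contradiction, because the text still fixes time as the random factor and names no other.

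A reader might infer more than the documents support:

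- *That the standard errors will be wrong.* This holds only if the text is fitted literally. Even then, one setting (ICC 0.3, slope SD 0.25) gave a ratio of 1.02, and the direction elsewhere depends on variances that the document does not give.
- *That the plan leaves out a fixed time trend.* Nothing in the text excludes one, and an article may leave that detail to the full plan.
- *That AIC or BIC will decide whether the slope is dropped.* The article says only that they assess model fit. Starting with an intercept and then considering a slope is common model building.
- *That the main result is at risk.* Objective 2 concerns the experimental arm only, gaze performance is a secondary outcome, and no formal test is stated for it. The between-group hypothesis is tested by ANCOVA.

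**Conclusion.** The point holds as a self-contradictory specification: the random factor named does not do what the model is chosen to do. If fitted as written, the intraclass correlation would answer the wrong question. The SE of the trend would range from about 23% too small to 81% too large over the assumed grid, with type I error of about 0.1% to 13.5% and more if participants' slopes differ more widely. These sizes rest on assumed variance components, complete data and a literal fit. A participant-level model was probably intended, so the error in the results is possible, not established. The ANCOVA comparison and the totals of 46 and 56 do not change. This is a moderate correction to one of the two stated objectives.

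**What to change.** Restate the objective 2 model along these lines: a linear mixed model for gaze performance in the experimental group, with time as a fixed effect and participant as the grouping factor, including a random intercept and a random slope for time by participant. State that the intraclass correlation is reported at participant level. AIC and BIC can stay as measures of fit.

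The cost is wording and, if the code follows the present text, a change to the grouping term. No extra data are needed. The interval for the mean trend may widen when participants improve at different rates, which then reflects the real uncertainty.

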## Results

Enrollment for this study was started in August 2014. To date, 36 participants have been enrolled. There have been 6 drop-outs. It is expected that the study will be completed by January 2016 and the first results are expected to be submitted for publication in spring of 2016.

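### Recruiting 56 with 20% attrition leaves about 45 participants, not the 46 the plan requires (a minor arithmetic error)

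*Protocol article*

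**What the plan says.** All the inputs are in the last paragraph of Statistical Analysis and Power Assessment in the protocol article:

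- Effect: "The pilot data showed a standardized effect size of .80". No outcome is named.
- Covariates: "Assuming the number of model covariates to be 3, the proportion of variance explained by these covariates to be 10" percent.
- Test: "a two-tailed test of the null hypothesis of no group difference at alpha=.05".
- Result: "we calculated that a sample size of 46 is required".
- Recruitment: "Given an expected attrition rate of 20% over the study observation period for objective 2, we propose to recruit a total of 56 individuals", split equally between the two groups.

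Neither the target power nor the formula that leads from 46 to 56 is given. The Abstract, the Recruitment section and the section on randomization and blinding repeat 56 without further derivation. The Results section reports progress: "To date, 36 participants have been enrolled. There have been 6 drop-outs".

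The same statistical section specifies the between-group analysis as an analysis of covariance of the postintervention measurement, adjusted for the preintervention measurement. Objective 2, listed at the start of Methods, concerns the time course of gaze performance among participants in the home program only.

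**The concern.** An attrition rate is a fraction of those recruited. The number to recruit is therefore the number needed divided by the fraction expected to remain. Multiplying the number needed by one plus the rate gives too few, because the loss then falls on the inflated total. The stated 56 looks like the product of that shortcut.

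What is at stake is whether the recruitment target delivers the sample that the plan says it needs. A reader of this paragraph will assume that 56 secures 46 under the expected loss, and no other part of the article justifies 56.

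There is also a point of wording. The sentence ties the attrition to objective 2, which involves one arm, while the total being inflated comes from the comparison of both arms.

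**Working it through.** **Inputs from the document.** d = 0.80; k = 3 covariates; R² = 0.10; two-sided alpha = 0.05; required total 46; attrition 20%; recruitment 56 in equal groups (28 per arm).

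**Input assumed.** Power of 80%, because none is stated and 80% is the conventional level that returns 46. With the same inputs, 85% would give 52 to 53 and 90% would give 60 to 62.

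**1. Reproducing the 46.** With the normal approximation, n per arm = 2 (1.960 + 0.842)² (1 − R²) / d² = 2 × 7.849 × 0.90 / 0.64 = 22.1, so 23 per arm and 46 in total. The 46 is reproduced.

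**2. Reproducing the 56.**
- Adding the allowance: 46 × (1 + 0.20) = 55.2, rounded up to 56. This matches the stated total.
- Dividing it out: 46 / (1 − 0.20) = 57.5, rounded up to 58 (29 per arm). This does not match.

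**3. What each total delivers at 20% loss.**
- 56 × 0.80 = 44.8, which is 1.2 below 46.
- 58 × 0.80 = 46.4.
- The largest loss at which 56 still leaves 46 is 1 − 46/56 = 10/56 = 17.9%.

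**4. Effect on power.** This uses the noncentral F test for the group effect with noncentrality N d² / [4 (1 − R²)] and N − 5 error degrees of freedom. At N = 46 the noncentrality is 46 × 0.64 / (4 × 0.90) = 8.18 on 41 degrees of freedom. N = 44.8 and N = 46.4 are expected numbers, not attainable sample sizes.

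| N analysed | Power |
|---|---|
| 44 | 77.9% |
| 44.8 (56 recruits, 20% loss) | 78.6% |
| 45 | 78.8% |
| 46 (stated requirement) | 79.7% |
| 46.4 (58 recruits, 20% loss) | 80.1% |

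On this more exact calculation, 47 is the first whole number that reaches 80%, so 46 has no slack.

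**5. Chance of retaining at least 46.** If each participant drops out independently with probability 0.20 (an assumption), 56 recruits leave 46 or more with probability 0.42, and 58 recruits do so with probability 0.63.

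**The case against.** The strongest reply is that the gap is trivial: two recruits, 1.2 expected completers and 79.7% − 78.6% = 1.1 points of power, in a pilot trial whose effect size is itself a pilot estimate. This stands as an argument about severity. It does not make the stated figure right.

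A second reply is that the attrition phrase refers to objective 2, so objective 1 may not need the allowance. It may only name the period over which loss is expected. The phrase is unclear, but neither reading rescues the 56. Attrition is the only reason given for moving the two-arm total from 46 to 56, and the 46 was calculated for the between-group test.

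A third reply is that the article does not define a drop-out as a missing postintervention assessment, nor say how missing data are handled for objective 1. That is fair, and such detail may be in a document not shown. The effect on the analysis is therefore conditional: a participant without a postintervention value supplies no outcome to the analysis of covariance as described. Only the objective 2 model is said to use all available data.

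A fourth reply is that observed loss is below the limit: 6/36 = 16.7%, and at that rate 56 × (1 − 6/36) = 46.7 would remain. This neither removes the error nor adds to it. The article does not say how many of the 36 have finished, so the final rate could be higher.

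**Conclusion.** Wrong as written, and minor. Under the plan's own 20% attrition, 56 recruits leave about 45 participants and not 46; the total that corresponds to 46 is 58. This rests on three figures in one paragraph and needs no assumption about power. That the 56 came from 46 × 1.2 is inferred, but the mismatch holds however it was reached.

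The cost in power, about one point, rests on the plan's inputs and on the noncentral F calculation above.

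A reader might infer that the trial misses its planned power for every primary outcome. The documents do not support that. No target power is stated, and the calculation is not tied to dynamic visual acuity, balance or the dizziness inventory. By the more exact method, 46 itself falls just short of 80%. Nor do the documents show that the shortfall will occur, since it depends on final attrition exceeding 17.9%.

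**What to change.** Keep 56 and correct the sentence so that it:

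- says that 20% attrition leaves about 45 participants with a postintervention value, giving about 79% power for a standardized difference of 0.80 with three covariates explaining 10% of the variance and two-sided alpha of 0.05, against 79.7% at 46;
- notes that 58 is the total that corresponds to 46 under 20% loss;
- states the power level for which the 46 was calculated;
- says that the allowance applies to the two-arm comparison of objective 1, and not only to objective 2.

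The cost is a small rewording in one paragraph, and a stated power about one point less favourable. Recruitment does not change. Raising the target to 58 would instead mean two more participants and changing 56 wherever it is repeated, with 36 already enrolled; the size of the error does not demand that.
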